### Data management procedures

Data management procedures for this incentives trial are the same as for the main IPSAZ study, and are described elsewhere
^
24
^.

### Ethics and dissemination

Ethical approval for the IPSAZ study protocol, including the incentives trial, has been provided by the Medical Research Council of Zimbabwe (MRCZ/A/2899), the London School of Hygiene & Tropical Medicine Research Ethics Committee (26787), and the Biomedical Research and Training Institute Institutional Review Board (AP176/2022).

Written informed consent to participate in the main IPSAZ study will be obtained in either English or Shona, depending on participant preference. This will include from pregnant minors, who are considered emancipated in Zimbabwe.

Importantly, although participants will be counselled on the benefits of PN, it is recognised that participants may have valid concerns about disclosing this information to partners, in terms of risk of relationship breakdown or intimate partner violence. As a result, we will support participants in coming to their own decision on whether to inform their partner or not.

Adverse events will be documented and discussed at regular debrief sessions. This will include any instances of harm to either indexes or their partners, as a result of the partner notification process. This includes some of the potential negative consequences that we will routinely collect from participants during follow-up, including verbal, physical, sexual, or other abuse. For participants reporting abuse, the needs of the participant will be discussed as part of a multi-disciplinary team at the clinic. Referral processes will be integrated into existing clinic processes as much as possible. Possible onward referrals include to governmental sexual and gender-based violence clinics, charitable organisations focussed on intimate partner violence, counselling services, and/or the police, if required. Additionally, if the participant is under the age of 18 years, referral to social services will be considered. 

Adverse events may also be reported to the Medical Research Council of Zimbabwe if warranted, for example due to severity.

Results will be submitted to open-access peer-reviewed journals, presented at academic meetings and shared with participating communities and with national and international policy-making bodies.

## Discussion

There has been a significant push towards development and integration of new diagnostics for STIs into health systems in the Global South. Importantly however, without concurrent improvements in the key tenets of STI management, namely risk reduction counselling, condom use, and effective partner notification and treatment, the potential benefits of aetiological diagnosis may be limited. One strategy that may help to support partner services is the use of incentives, which may be financial or non-financial. In both instances, the aim is to nudge the partner so that they are more likely to attend a clinic for treatment. However, particularly for financial incentives, they may also improve the likelihood of an index patient informing a partner, if it makes them feel more able to deliver ‘bad news’ if accompanied by something beneficial.

We have chosen $3 (USD) based on input from key stakeholders, from an initial potential range of $1 to $10. An important factor in choosing $3 was that we hoped this would facilitate partners to attend, but not induce them. From an ethical perspective, there is a risk of coercion with larger incentives in socioeconomically deprived communities. Given that PN may carry a risk of violence or relationship breakdown, it is important that the incentive does not force women to inform their partners due to the size of the incentive, against their better judgement
^
6
^. Importantly, as the direct beneficiaries of the incentive are the partners, we anticipate this is less likely compared to if the incentive was directly benefitting the index. Additionally, it will be emphasised to the intervention team that pregnant women should be supported in coming to the right decision for them, which may be not notifying their partner if there is a risk of negative repercussions.

A further consideration is that higher incentives, although likely to be more effective in research settings, are less likely to be implemented in practice in resource-limited health settings. A one-off payment of $3 could be a programmable intervention, and also be more equated to a ‘nudge’ compared to $5 or $10 which are more akin to direct payments. If found to be successful, other mechanisms to enhance sustainability will need to be considered. For example, they could be used as an entry point for HIV testing for this high-risk group, or other interventions.

Another important decision was the PN strategy to be used. There is currently no consensus on the most appropriate PN strategy, and ideally this should be tailored to the particular setting
^
5,
35
^. Client referral will be used in this study, largely due to what is likely to be feasibly implemented in routine practice in the future. In Zimbabwe, chronic staff shortages make more resource-intensive PN strategies much less likely to be implemented.

Importantly, although a shift to aetiological testing will bring a host of advantages to STI management in Southern Africa, it will also bring some additional challenges. Given that syndromic management has been in place for decades, a cultural shift will be required for both clients and healthcare workers, towards an understanding of asymptomatic infections, and the need for screening and treatment. This may have ramifications for PN, with the potential for reluctance if neither index patient not partner have symptoms. This was raised in a mixed methods study in Gaborone, Botswana, where a lack of symptoms was noted as a barrier for index cases to inform their partners, as they did not think their partner had an infection
^
15
^. The difficulty of explaining that someone might have an infection without symptoms was raised. Furthermore, general trust in health systems and health providers will also inform these decisions. Incentives and other methods to promote PN will therefore be important in facilitating this shift.

A key strength of this study is that the intervention has been tailored and informed based on input from key stakeholders. Additionally, although sample size calculations were not performed with this trial in mind, it will likely be moderately powered to detect clinically significant differences in PN uptake.

Important limitations relate to generalisability. Firstly, this study will be conducted in urban PHCs in Harare. Results are likely less generalisable to rural settings, where distance to nearest clinic, availability of transport, expected quality of care, and socioeconomic differences, may alter the perception of such an incentive. Secondly, this is an ANC study, which is unique for several reasons; 1) All indexes will be pregnant women; 2) most if not all partners will be male; 3) the health and wellbeing of the baby will likely be an important factor in decision-making; and 4) there may be a higher proportion of stable relationships compared to other settings. These unique circumstances mean that any attempts at extrapolating these findings to other settings or sub-populations must be done so with a high level of caution.

A further limitation is that our primary outcome is based upon at least one partner returning for treatment. This does not take account of index cases with more than one sexual partner. However, demographic health and survey data from Zimbabwe reported that less than 1% of surveyed women and 2.5% of surveyed men reported concurrent sexual partners in the preceding 12 months
^
36
^. Furthermore, as data on both number of partners and number of partners treated will be collected, we will be able to make an assessment of the degree to which partner notification was successful in index cases with multiple partners
^
37
^.

Finally, all clients and their partners receive treatment free of charge in this study, which is not representative of clinic settings in Zimbabwe, where fees and co-payments are standard. This may therefore influence how we interpret differences between groups, as even in the control arm, an important barrier to access has already been removed. Additionally, as treatment is available from most PHCs, there is a risk that partners may attend the PHC most convenient to them, and thus not be included as a study outcome. However, providing treatment free of charge in the control arm will reduce this risk.

As far as we are aware, this is the first randomised controlled trial to assess the effect of a small financial incentive on PN for STIs. It will provide important data on the potential for the use of financial incentives to improve uptake of PN in urban, Southern African settings. Although it will not replace the need for cohesive and funded PN strategies tailored to the population served, incentives may enhance baseline uptake, allowing for reduced rates of re-infection and their associated complications.

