### Proposed intervention

As per standard of care, partners will be notified by client referral. Post-test counselling to participants diagnosed with an STI or treated for a syndrome will include the importance of partner treatment. They will be provided with PN slips for their partners to return for presumptive treatment. Index cases can receive as many PN slips as they require. Partners who attend the study clinic and present their PN slip will be provided with presumptive treatment free-of-charge. Partners will be considered lost-to-follow up if they have not returned within 28 days after treatment of the index case.

The intervention will be provision of $3 (USD) provided to a partner on returning to the clinic for treatment. The amount was based on in-depth interviews with pregnant women, male partners, and midwives, recruited when attending or working at one of the intervention clinics, as well as discussions with members of the intervention team. Questions on appropriate incentive value were embedded within broader discussions about PN, including different methods of PN, associated challenges, and feasibility of PN. Specifically for incentives, stakeholders were asked what they thought about the idea, any potential negative consequences, and what a suitable value would be for an incentive. Male partners often noted that an incentive should cover cost of travel, but also leave the partner with some additional money to spend. In contrast, pregnant woman and midwives tended to say any financial incentive, even very small, would prompt partners to attend. They also noted that unintended consequences could include using the incentive for alcohol or drugs, or for individuals who were not the index’s real partner to attend. A compromise value of $3 was therefore chosen, with a key factor being that $3 covers a return journey by public transport from the majority of locations from where pregnant women (and therefore potentially their partners) are likely to travel.

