### Randomisation and blinding

Randomisation of each clinic day will be performed in a 1:1 ratio between days where issued slips are associated with an incentive and days where no incentive is issued. Randomisation by clinic day was chosen as a method to allocate incentives, in preference to individual randomisation, to prevent contamination. Additionally, if some individuals presenting on the same day were offered an incentive and others were not, this may lead to a greater perception of unfairness amongst participants.

Randomisation will be performed by a statistician not involved in the IPSAZ study, using the formula “=INT(RAND()*2)” in Microsoft Excel for each clinic day. Randomisation outcomes will be recorded on a document produced for each month, and kept at each clinic site. The intervention team will refer to this document to determine whether it is an ‘incentive’ or ‘non-incentive’ day. For each individual pregnant woman, it will also be documented whether an issued PN slip was associated with an incentive or not. Similarly, when partners return it will be recorded if an incentive was provided. To ensure compliance with the randomisation log, this data will regularly be cross-checked to ensure that clients are being provided the correct slip based on day of attendance.

It is not possible to blind participants or researchers to the intervention. However, participants will only be informed of the availability of an incentive once they test positive on an incentive day and have already informed the clinical team how many PN slips are required. This is to prevent participants from providing an artificially elevated number of partners in order for incentives to be provided to individuals who are not actual partners of the index case. Of note, women could still return with a male who is not a sexual partner, and this would be difficult to detect. However, given the factors discussed regarding ensuring the health of the baby, and that this would still require disclosure of treatment to another male, we feel that the risk of this is low.

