### Outcomes

The primary outcome measure is the proportion of indexes with at least one partner who returns to the study site for partner services within 28 days of index diagnosis. Each PN slip will also have a unique ID that links partners to the index client, thus allowing for recording of this data. The main secondary outcome will be the number of days between index case diagnosis and the partner attending for partner services. Additional secondary outcomes will include uptake of PN slips by pregnant women, adverse birth outcomes in index cases, number of partners who receive treatment, and intervention cost. Number of partners who receive treatment will be recorded from our study antibiotic administration records, and compared with that reported by participants during telephone follow-up.

Furthermore, the proportion of indexes with at least one partner who returns to the study site for partner services any number of days from index diagnosis, will also be measured as a secondary outcome.

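### Both the primary outcome and the count of treated partners see only the study clinic, where only incentive-arm partners are paid, so part of an observed effect could be moved attendance

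*Protocol article*

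**What the plan says.** All references are to the Protocol article.

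- **Outcomes.** The primary outcome is the proportion of indexes with "at least one partner who returns to the study site for partner services within 28 days of index diagnosis". Linkage is by the slip: "Each PN slip will also have a unique ID that links partners to the index client". A further secondary outcome drops the 28-day limit but keeps the study site. On treated partners: "Number of partners who receive treatment will be recorded from our study antibiotic administration records, and compared with that reported by participants during telephone follow-up".
- **Proposed intervention.** "The intervention will be provision of $3 (USD) provided to a partner on returning to the clinic for treatment". Free care is offered whichever slip is held: "Partners who attend the study clinic and present their PN slip will be provided with presumptive treatment free-of-charge".
- **Randomisation and blinding.** Whether a slip carries the incentive depends on the randomised clinic day.
- **Discussion.** Because most primary clinics can treat, "there is a risk that partners may attend the PHC most convenient to them, and thus not be included as a study outcome". The reply is "However, providing treatment free of charge in the control arm will reduce this risk". The same paragraph says that all clients and partners in the study are treated free and that patients in Zimbabwean clinics ordinarily pay.
- **Main study procedures.** Every woman is telephoned after birth and asked, among other things, whether her partners were treated. No restriction to the study clinic is stated.

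**The concern.** The Discussion treats care elsewhere as a general loss of outcomes. It does not say that the loss may differ between arms. A partner who would be treated in either case has one more reason to choose the study clinic if his slip carries $3. The amount was chosen largely because it covers the return fare for most journeys, and distance is an obvious reason to use a nearer clinic. The payment therefore acts directly on whether a treated partner is seen by the study.

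If some partners are drawn from other clinics, the primary outcome rises in the incentive arm while the number of partners treated stays the same. The secondary count from study antibiotic records would rise with it, because it has the same restriction of place. At stake is the interpretation: the article's closing paragraph links better uptake to less re-infection, and moved attendance would not deliver that.

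**Working it through.** **1. The plan's own figure, as a yardstick.** Inputs from Sample size calculations: control proportion 30%, alpha 0.05 (sidedness not stated; two-sided reproduces the figure), power 0.80, ICC 0, and 100 clusters × 1.5 = 150 indexes per arm.

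- An odds ratio of 1.96 on 30% gives (0.30 × 1.96) / (0.70 + 0.30 × 1.96) = 0.588 / 1.288 = 0.457.
- With pooled variance, n = [1.96·√(2·p̄·(1−p̄)) + 0.842·√(p₁(1−p₁) + p₂(1−p₂))]² / (p₂−p₁)². This gives 150 per arm.
- Solved for the odds ratio at n = 150, the result is 1.958, against 1.96 in the article. With ICC 0.10 the design effect is 1 + 0.5 × 0.10 = 1.05 and the result is 1.990, against 1.99.

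The sample size figures are sound. The detectable difference is 45.7% − 30% = 15.7 percentage points.

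**2. Displacement with no change in partners treated.** Let e be the proportion of control indexes whose partner is treated elsewhere, and f the share of these that the $3 moves to the study clinic. The documents give neither, so both are assumptions. Total treatment is 30% + e in both arms. The incentive arm's primary outcome is 0.30 + e·f, and the odds ratio is that proportion's odds divided by 0.30/0.70.

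| e | f | Incentive v control | Odds ratio | Chance of a significant result favouring the incentive |
|---|---|---|---|---|
| 5% | 50% | 32.5% v 30% | 1.12 | about 7% |
| 10% | 50% | 35% v 30% | (0.35/0.65)/(0.30/0.70) = 1.26 | about 15% |
| 10% | 100% | 40% v 30% | (0.40/0.60)/(0.30/0.70) = 1.56 | about 44% |
| 20% | 75% | 45% v 30% | 1.91 | about 77% |

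To produce the whole detectable odds ratio of 1.96, displacement alone would have to reach 15.7 points.

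**3. Which planned measures could show this?** Return within 28 days, return at any time, and the study-record count of treated partners all stop at the study clinic. Only the woman's report at the post-natal call could capture treatment elsewhere. The article uses it as a comparison for the record count and does not name treatment anywhere as an outcome.

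**The case against.** The case for leaving the plan alone has real weight.

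- **The quoted sentence is not false.** It claims only to reduce the risk. A control partner who goes elsewhere usually gives up free care for a fee, so he too has a financial reason to bring his slip to the study clinic. This stands, and it is why losses are probably modest. It does not show that they are equal between arms, because free care is common to both and the $3 is not.
- **The outcome matches the aim.** Drawing partners to the clinic by easing transport cost is the intended mechanism, and a record-based primary outcome is objective. This also stands. Read strictly as study-clinic attendance, the primary outcome measures its target directly. The difficulty arises when the result is read as more partners treated.
- **Telephone reports are already collected, and tabulation by arm may be left to an analysis plan.** A reader might infer that the record-versus-telephone comparison will be made only overall. The article does not say that; it does not state whether the comparison is by arm. The point rests instead on the stated outcomes all stopping at the study clinic and on the mitigation offered in the Discussion.
- **Non-partners.** A reader might add that payment encourages sending someone else, since "women could still return with a male who is not a sexual partner, and this would be difficult to detect". The article discloses this, has women state how many slips they need before they learn of the incentive, and gives reasons for judging the risk low. The safeguard is partial, but the documents do not support treating substitution as an established bias.

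**Conclusion.** The point holds as a limit on interpretation. Partners treated at other clinics are missed by the primary outcome and by the study-record count of treated partners. The stated mitigation lowers that loss in both arms without removing a possible difference between them, and any such difference would favour the incentive.

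The size is unknown. If 10% of control indexes had a partner treated elsewhere, which is a quarter of all treated in that arm (10 of 40), odds ratios of 1.26 to 1.56 could arise with no extra partner treated. At 5% with half moved, the effect is slight (1.12). A reader might infer that a positive result would be merely an artefact. The documents do not support that: they give no rate of treatment elsewhere, fees elsewhere argue against a high one, and 15.7 points of displacement would be needed to mimic the full detectable effect.

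**What to change.** 1. Pre-specify a secondary outcome, compared by randomised arm over all indexes given a PN slip: at least one partner treated anywhere, from the study record or the woman's report at the post-natal call. The article gives no sign that the call dates the treatment, so this outcome has no 28-day window. Its natural companion is the existing any-time return outcome.
2. Tabulate disagreement between record and report by arm, with the number of calls completed. The informative cell is record no/report yes, a sign of treatment elsewhere. Record yes/report no is not a reliable flag for non-partners, since a woman who sent someone else may still report her partner as treated.
3. Amend the Discussion sentence to say that free treatment lowers the loss in both arms and that what remains may differ by arm.
4. Interpret the primary result as study-clinic attendance, alongside the new outcome. Do not make a claim conditional on the two agreeing in direction: an unpowered self-report could then overrule a true effect.

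The cost is wording and one extra analysis, because the question is already in the call. The weakness is that the report is late and unblinded and some calls will be missing, which would leave some treatment elsewhere uncounted. The outcome should therefore stay secondary and supportive.

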## Data Availability

No data is associated with this article. Following publication of study results, the subset of data required for the purposes of verifying research findings will be made available for sharing and will be placed in Data Compass (the London School of Hygiene & Tropical Medicine institutional research data repository—accessible at
https://datacompass.lshtm.ac.uk/). This repository will enable direct download of records with codebooks to enable replication of the data analyses. A more complete sharing of data with any research group requesting access to individual data records will be done 12 months after publication. At this point, all data and study tools will be made available through Data Compass. Data for sharing will be de-identified prior to release. Details of how to access data will be published with each study publication.
